### Inclusion procedure

2.2

The principal investigator will screen and exclude participants with abnormalities in oral structures based on speech assessments. A comprehensive list of eligibility criteria is presented in Table 1. Stroke specialists will identify participants with dysarthria using the National Institute of Health Stroke Scale (NIHSS) criteria (23). The NIHSS is utilized for its ease of administration and standardized approach, which minimizes interpersonal variation in assessments. Also, the sub-section of “10. speech” is suitable for initially identifying dysarthria severity in stroke patients. We aim to recruit participants with both mild-to-moderate and severe dysarthria. Mild-to-moderate dysarthria is characterized by slurred speech that remains understandable, and severe dysarthria involves mostly unintelligible speech or the inability to speak without evidence of aphasia. The eligible participants will be referred to a research coordinator to verify their suitability for the trial. To educate the participants, the principal investigator will provide detailed information about the study, such as intervention options, associated risks, and expected benefits. All recruitment and screening processes will be thoroughly documented.

Participants will be clearly informed that they have the right to withdraw from the study at any point without any consequences to their future medical care. Withdrawal criteria will include voluntary withdrawal by the participant, a usage rate falling below 40%, a need for immediate medical care that precludes continued participation, and any adverse events that are directly related to the digital therapy application. Additionally, the research team reserves the right to withdraw participants if there is significant noncompliance with the study protocol or if their health status changes to the extent that continued use of the application is deemed unsuitable or unsafe.

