### Outcome measurements

2.6

The study will span 4 weeks, and the details are provided in Table 2. Three assessment stages will be conducted during the process.

**Table 2 tab2:** Schedule of enrollment, interventions, and assessments.

	Enrollment	Randomization and allocation	Post-allocation		Close-out
Timepoint	Pre-baseline		Baseline	4 weeks	Post-study
Enrollment					
Eligibility screen	X				
Informed consent	X				
Allocation		X			
Interventions					
Conventional speech therapy					
Digital speech therapy application					
Assessment					
Speech intelligibility			X	X	
Percentage of consonants correct			X	X	
Oral diadochokinetic			X	X	
Maximum phonation time			X	X	
Depression			X	X	
Quality of life			X	X	
System usability					X

Demographic and clinical characteristics will be recorded after enrollment in the study. This initial recording includes demographic data (age and sex), medical history, stroke information (type and location of stroke and post-stroke duration), level of impairment measured using the NIHSS (23), cognitive status determined using the Korean Mini-Mental State Examination (K-MMSE) score (20), and Clinical Dementia Rating (CDR) tests (36). The demographic and clinical characteristics of the participants are shown in Table 3.

**Table 3 tab3:** Variables evaluated at baseline and study period.

Components	Subcategories
Age	Years
Gender	Male / Female
Medical history	Medication history, concomitant disease history (for example, dementia [Alzheimer’s disease, vascular dementia], central nervous system infection [e.g., human immunodeficiency virus, syphilis, Creutzfeldt-Jakob disease], Pick’s disease, Huntington’s disease, Parkinson’s disease, and others).
Medication	Details of concomitantly administered drugs (for example, medications for dementia treatment, central nervous system stimulants, anticholinergics, tricyclic antidepressants, typical antipsychotics, sleeping pills, typical antipsychotics, anxiolytics, antidepressants, and thyroid hormone)
Type of stroke	Ischemic/hemorrhagic
Stroke lesion location	Cortical (for example, frontal, parietal, and so on), subcortical, cerebellum, thalamus, basal ganglia, and so on.
Side of stroke involvement	Left/Right
Time to enroll after stroke	In days
Cognitive function	Korean Mini-Mental State Exam, Clinical Dementia Rating
Neurological status	National Institute of Health Stroke Scale
Visual function	Intact/Non-intact
Hearing function	Intact/Non-intact
Aphasia	Yes/No

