Subsequently, the participants will undergo a comprehensive assessment for post-stroke dysarthria. Psychological well-being questionnaires will also be administered to assess depression and quality of life. Participants will engage in the post-evaluation phase 4 weeks after the baseline assessment. We will repeat the speech assessments and psychological questionnaires from the baseline evaluations. Additional evaluations of usability and adherence rates will be conducted.

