#### Feasibility

2.6.2

A comprehensive evaluation will be conducted to assess the feasibility of this trial. First, the trial will estimate the number of potential participants, the duration of recruitment, and the success rate of screening to secure a representative sample size. Additionally, retention rates will be monitored throughout the trial. These measurements will ensure a rigorous sample size for future studies. Second, the participants’ adherence to digital therapy applications will be measured. This will include tracking the frequency and completeness of the application usage and participant engagement with the treatment protocol using a robust data collection and management system. Third, participant feedback will be collected to assess the acceptability and effectiveness of the digital therapy. We will use the System Usability Scale (SUS) questionnaire to measure the usability of the digital speech therapy application in terms of efficiency and user satisfaction (44). Additionally, interviews will be conducted with the application user to collect qualitative insights such as participants’ experiences, challenges, and suggestions for improvement. This comprehensive feedback will aid in a better understanding of the application’s usability and effectiveness and contribute to future development and enhancements. Finally, we will monitor patient safety and potential adverse events and uphold ethical standards. Digital speech therapy applications include the real-time monitoring of patient log data to swiftly identify and address usage errors or technical issues. Rigorous testing of the application’s performance will also focus on stability and user interface to assess its impact on therapy effectiveness and user experience. This approach ensures the safety and reliability of the digital tools throughout the study.

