### Analysis

2.7

The primary objective of this trial is to investigate the non-inferiority of the intervention group compared to the control group in terms of changes in speech intelligibility from baseline to post-treatment. The hypothesis is as follows:

$$H_{0}:\mu_{t}-\mu_{c}<\delta \;vs\;H_{1}:\mu_{t}-\mu_{c}\geq \delta$$

Where *μt* is the mean change in speech intelligibility score in the intervention group using the digital speech therapy application, and *μc* is the mean change in the control group receiving conventional speech therapy. It is assumed that there is no difference between the two groups, and this study seeks to establish the non-inferiority of the groups. The non-inferiority margin *δ* is set at 19 points, based on the assumption that a difference of 1 to 19 points on the speech intelligibility scale is clinically non-inferior (45).

The sample size required for the non-inferiority trial was determined using a statistical formula (46). This involved setting the significance level (alpha) to 0.025 for a one-sided test and targeting a power of 80% (*β* = 0.2) (47) with a standard deviation of 24.9 (48). This calculation revealed that 28 participants are required for each group. A total of 56 participants are required for the trial. To account for a possible dropout rate of 30%, we aim to recruit a total of 76 participants, with 38 participants in each group.

$$n=\frac{2{\left(z_{\alpha }+z_{\beta }\right)}^{2}\sigma^{2}}{{\left(\mu_{t}-\mu_{c}-\delta \right)}^{2}}\approx 28$$

Analyses will be performed using SPSS software (version 27; IBM Corp., Armonk, New York). Descriptive statistics will summarize the demographic data and outcome measures. For interval estimates, 95% confidence intervals will be provided. An intention-to-treat (ITT) analysis will include all randomized participants. Additionally, we will conduct a per-protocol (PP) analysis which includes only participants who fully adhered to the intended protocol.

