Maintaining long-term commitment to post-stroke treatment can be challenging (58, 59). Patients may exercise less frequently than suggested (60), struggle to achieve daily treatment goals (61), or discontinue therapy entirely (59). Digital solutions offered for comfort in patients’ homes are expected to encourage more intensive speech treatment (6) and better adherence. Digital speech therapy applications enable easier access to speech therapy, increase engagement, and may reduce costs (62, 63). However, this study has several limitations. First, the limited sample size might limit the applicability of our results. Second, our digital speech therapy application is designed exclusively for Koreans and targeted at native Korean speakers. This language limitation could limit the generalizability to non-Korean populations. Third, the lack of direct supervision by clinicians or SLPs in digital speech therapy interventions could affect patient motivation and result in higher dropout rates (59, 64). Finally, a significant challenge arises from the high proportion of older participants, which is typical in stroke patient demographics (65). Despite considering the design of our application for the elderly population, these participants may experience lower usability and adherence to digital treatment because of their unfamiliarity with digital technology.

Despite these limitations, this study has several strengths. First, it aims to provide new evidence for the use of digital speech therapy in the treatment of post-stroke dysarthria. This could increase the adoption of digital treatment in the field. Second, the study is designed to investigate whether a digital speech therapy application is effective and feasible for stroke participants, regardless of their severity and recovery stage.

In conclusion, this trial explores the efficacy and feasibility of digital speech therapy applications in treating post-stroke dysarthria. Our study aims to provide significant insights that will aid future research by refining effect size estimates and enhancing power analysis. By addressing the complexities of post-stroke speech therapy through a digital application, we expect to enhance treatment strategies. Through our trial, we expect to be able to provide evidence of digital therapeutics for the treatment of post-stroke dysarthria.

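### The System Usability Scale is scheduled only at close-out, with no collection shown at early stop, so the usability result is at risk of completer bias

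*Protocol article*

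**What the plan says.** Section 2.6.2 (Feasibility) names the instrument: "We will use the System Usability Scale (SUS) questionnaire to measure the usability of the digital speech therapy application". It also plans a qualitative component: "interviews will be conducted with the application user to collect qualitative insights such as participants’ experiences, challenges, and suggestions for improvement". It gives no timepoint for either.

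Timing appears in two places in section 2.6. In Table 2 the row "System usability" has one mark, in the close-out (post-study) column; its baseline and 4-week cells are empty. The text after Table 3 says "Participants will engage in the post-evaluation phase 4 weeks after the baseline assessment", describes the repeat speech and questionnaire measures, and adds "Additional evaluations of usability and adherence rates will be conducted". The interview is not in Table 2.

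Three other statements bear on who will still be present to answer. Section 2.2 (Inclusion procedure) includes among the withdrawal criteria "a usage rate falling below 40" per cent. Section 2.7 (Analysis) sets recruitment at 38 per group with the words "To account for a possible dropout rate of 30" per cent. The Discussion says of older participants that "these participants may experience lower usability and adherence to digital treatment because of their unfamiliarity with digital technology".

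**The concern.** Usability is one of the results the trial promises, and section 2.6.2 uses the SUS and the interview to judge acceptability and to guide further development of the app. People who give up on the app, or whose use falls so low that they are withdrawn, plausibly find it hardest to use. If the only scheduled SUS comes after they have left, the missing scores are missing for a reason closely tied to what the scale measures. The mean would then describe those who stayed and would look better than the experience of everyone assigned to the app.

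The missing-data methods in section 2.7 would not repair this. With one SUS timepoint there is no earlier value to carry forward. Multiple imputation would have to predict stoppers' scores from completers' scores. If the usage rule is applied as written, few or no observed scores would come from the low-usage range, so the imputation would be extrapolation.

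**Working it through.** **The plan's own figure.** The article states no expected SUS value, so there is none to reproduce. The one calculation that supplies an input here, the sample size, does reproduce. With margin 19, SD 24.9, true difference 0, one-sided alpha 0.025 and 80% power, n = 2 × (1.960 + 0.842)² × 24.9² / 19² = 26.96, so 27 per group by the normal approximation. The t-based calculation gives 28 (power 0.801), as stated. The planned 38 per group is taken as given.

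**Inputs.**
- App arm: 38 (section 2.7).
- Dropout fraction d: 0.30 (section 2.7), varied from 0.10 to 0.40.
- SUS gap g, completers' mean minus stoppers' mean: 10, 20 or 30 points. This is assumed; the documents give no value.
- No early stopper supplies a SUS score, which is the schedule as shown.

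**Formula.** With completers' mean C and stoppers' mean S, the mean over all app users is (1 − d)C + dS. The reported mean is C. The overstatement is C − [(1 − d)C + dS] = d(C − S) = d × g.

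| Dropout d | Without a score (38 × d) | With a score | g = 10 | g = 20 | g = 30 |
|---|---|---|---|---|---|
| 10% | 3.8 | 34.2 | 1.0 | 2.0 | 3.0 |
| 20% | 7.6 | 30.4 | 2.0 | 4.0 | 6.0 |
| 30% (stated allowance) | 11.4 | 26.6 | 3.0 | 6.0 | 9.0 |
| 40% | 15.2 | 22.8 | 4.0 | 8.0 | 12.0 |

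If one uses the loss implied by recruiting 38 to retain 28, d = 10/38 = 26.3%, and the overstatement is 2.6, 5.3 or 7.9 points. The picture is the same.

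**What partial collection would gain.** Suppose half of the stoppers answer when asked. Scores then come from 26.6 completers and 5.7 stoppers, and the stoppers' share is 5.7 / 32.3 = 17.6%. At g = 20 the unweighted mean is too high by (0.300 − 0.176) × 20 = 2.5 points instead of 6. Reporting the two groups separately lets a reader reweight to 70:30, which removes the remainder if the responding stoppers are typical of all stoppers.

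**Timing, side by side.** Table 2 has separate 4-week and close-out columns and marks usability only in the second. The text mentions usability within its account of the 4-week post-evaluation. The two do not place the SUS in the same column of the schedule.

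**The case against.** The strongest reply is that this is a journal article condensing a fuller protocol. Early-termination procedures are often left to that document, and nothing in the article bars asking a withdrawn participant for the SUS. That is fair and keeps the point modest. It does not remove it, because the schedule that is shown fixes one SUS timepoint at the end.

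A reader might infer three stronger things, and the article supports none of them:
- *That early stoppers are never asked anything.* Section 2.5.1 has researchers contact participants when app use falls and ask why. That contact is meant to re-engage people; it is neither the SUS nor a listed feasibility outcome. But it does ask declining users for their reasons.
- *That the interview is confined to completers at the end.* No timepoint is given, and it is described as for the application user. Equally, nothing assures that stoppers are interviewed.
- *That the whole feasibility conclusion rests on those who stayed.* Section 2.6.2 also covers recruitment, screening success, retention, adherence tracked from app use, and safety. Retention counts leavers directly, and tracked adherence needs no final visit.

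On size, the SUS gap has no source in the documents. The 30% is an overall planning allowance, not a forecast for the app arm, and some listed withdrawal reasons, such as a need for medical care, have nothing to do with usability. The article states no SUS threshold, so a shift of a few points is not shown to change a decision. The Discussion already concedes that usability, adherence and dropout may suffer. All of this stands.

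The timing mismatch is also small. Post-study follows directly on week 4 of a 4-week study, so the two places can be read together.

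**Conclusion.** The point holds for the usability and acceptability result only. As shown, the SUS is scheduled once, at close-out, with no collection at early stop, in a plan that lists low usage as a withdrawal criterion and allows for 30% dropout. The reported mean SUS is therefore likely to come mainly from those who stayed. If about 11 of 38 app participants gave no score and would have scored 10 to 30 points lower, the mean would be 3 to 9 points too high.

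That range rests on the assumed gap, on applying the overall dropout allowance to the app arm, and on no stopper answering. The likely direction is clearer than the size. This is a worthwhile refinement, not a flaw that threatens the trial or its primary analysis. The difference between Table 2 and the text is a minor matter of wording.

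**What to change.** - **Collection.** State in section 2.6.2 and Table 2 that app participants who stop or are withdrawn early, for any reason, are asked to complete the SUS by phone at the time of stopping. State the timing of the planned interview and offer it at the same contact. The withdrawal criteria need not change for this.
- **Reporting.** Give the number with a SUS score out of all randomised to the app, and the SUS overall and separately for early stoppers and completers.
- **Timing.** Reconcile Table 2 (post-study) with the text of section 2.6 (4-week post-evaluation), so that the SUS has one stated timepoint for those who complete.

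The cost is about 11 short calls by existing staff, if dropout reaches 30% of the app arm, using a 10-item questionnaire already in the trial, plus a few lines of text. Some stoppers will decline, so the bias will be reduced but may not vanish. The mean SUS may look slightly less favourable.

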#### Outcomes

2.6.1

The primary outcome is the change in speech intelligibility following the intervention. Speech intelligibility is crucial for effective communication and reflects how well a listener understands a patient’s speech (37). Speech intelligibility will be calculated using a passage-reading assessment. Participants will be instructed to read a passage aloud comfortably and naturally using the application for assessment. The application will record their speech and automatically upload the recordings to a secure server. Next, three independent SLPs will listen to the recordings via a web system. After hearing the passage once, they will transcribe it as they understand it. We will compare these transcriptions with the original passages to calculate the percentage of correctly transcribed words. Each participant’s final score will be the average of the scores of all three evaluators (38).

For secondary outcomes, the study will assess the participants’ speech function and psychological well-being through voice recordings and surveys via the application. The SLPs will listen to the recorded voices of the participants and rate each speech function measure. The maximum phonation time (MPT) assesses the ability to sustain vowel sound (39). Oral diadochokinetic (DDK) rate evaluates the speed, regularity, and accuracy of articulatory movements, with performance quantified by the number of syllables repeated rapidly and accurately (31). The percentage of consonants correct (PCC) is determined by comparing transcriptions from word-reading tasks with the original text to objectively assess the accuracy of consonant sounds (32, 40).

Self-report questionnaires will be used to assess psychological well-being. The Patient Health Questionnaire-9 (PHQ-9) evaluates the severity of depressive symptoms (41). The Quality of Life in the Dysarthric Speaker (QOL-Dys) scale quantifies how dysarthria affects various aspects of life. It specifically assesses the impact on daily activities (42, 43). These measures provided vital insights into the effects of interventions on communication and psychological health.

#### Feasibility

2.6.2

A comprehensive evaluation will be conducted to assess the feasibility of this trial. First, the trial will estimate the number of potential participants, the duration of recruitment, and the success rate of screening to secure a representative sample size. Additionally, retention rates will be monitored throughout the trial. These measurements will ensure a rigorous sample size for future studies. Second, the participants’ adherence to digital therapy applications will be measured. This will include tracking the frequency and completeness of the application usage and participant engagement with the treatment protocol using a robust data collection and management system. Third, participant feedback will be collected to assess the acceptability and effectiveness of the digital therapy. We will use the System Usability Scale (SUS) questionnaire to measure the usability of the digital speech therapy application in terms of efficiency and user satisfaction (44). Additionally, interviews will be conducted with the application user to collect qualitative insights such as participants’ experiences, challenges, and suggestions for improvement. This comprehensive feedback will aid in a better understanding of the application’s usability and effectiveness and contribute to future development and enhancements. Finally, we will monitor patient safety and potential adverse events and uphold ethical standards. Digital speech therapy applications include the real-time monitoring of patient log data to swiftly identify and address usage errors or technical issues. Rigorous testing of the application’s performance will also focus on stability and user interface to assess its impact on therapy effectiveness and user experience. This approach ensures the safety and reliability of the digital tools throughout the study.

### Analysis

2.7

The primary objective of this trial is to investigate the non-inferiority of the intervention group compared to the control group in terms of changes in speech intelligibility from baseline to post-treatment. The hypothesis is as follows:

$$H_{0}:\mu_{t}-\mu_{c}<\delta \;vs\;H_{1}:\mu_{t}-\mu_{c}\geq \delta$$

Where *μt* is the mean change in speech intelligibility score in the intervention group using the digital speech therapy application, and *μc* is the mean change in the control group receiving conventional speech therapy. It is assumed that there is no difference between the two groups, and this study seeks to establish the non-inferiority of the groups. The non-inferiority margin *δ* is set at 19 points, based on the assumption that a difference of 1 to 19 points on the speech intelligibility scale is clinically non-inferior (45).

The sample size required for the non-inferiority trial was determined using a statistical formula (46). This involved setting the significance level (alpha) to 0.025 for a one-sided test and targeting a power of 80% (*β* = 0.2) (47) with a standard deviation of 24.9 (48). This calculation revealed that 28 participants are required for each group. A total of 56 participants are required for the trial. To account for a possible dropout rate of 30%, we aim to recruit a total of 76 participants, with 38 participants in each group.

$$n=\frac{2{\left(z_{\alpha }+z_{\beta }\right)}^{2}\sigma^{2}}{{\left(\mu_{t}-\mu_{c}-\delta \right)}^{2}}\approx 28$$

Analyses will be performed using SPSS software (version 27; IBM Corp., Armonk, New York). Descriptive statistics will summarize the demographic data and outcome measures. For interval estimates, 95% confidence intervals will be provided. An intention-to-treat (ITT) analysis will include all randomized participants. Additionally, we will conduct a per-protocol (PP) analysis which includes only participants who fully adhered to the intended protocol.

First, the Shapiro–Wilk test will assess of the normality of the distributions. Based on these results, the appropriate parametric (independent two-sample t-test) or non-parametric test (Mann–Whitney U test) will be chosen for between-group comparisons. Then, mixed repeated-measures analysis of variance (ANOVA) will evaluate the changes over time within subjects and between groups, with fixed effects for time, group, and their interactions. Mauchly’s test will check sphericity by applying the Greenhouse–Geisser, if necessary. For significant findings, Tukey’s HSD tests will conduct post-hoc analyses with Bonferroni correction to control for the overall type I error rate at 0.05. The benchmark for statistical significance is set at *p* < 0.05.

We will address missing data using multiple imputation techniques and the Last Observation Carried Forward (LOCF) method. This approach aims to minimize bias and ensure the robustness of efficacy outcomes (49). Subgroup and sensitivity analyses will be conducted to explore the effects of participant characteristics and institutional factors on the primary efficacy results. In addition to the primary analysis, we will conduct subgroup analyses to examine the efficacy of our digital speech therapy application in various settings. Subgroup analyses include comparing its use during hospitalization with post-discharge home use. These analyses aim to provide a deeper understanding of how the setting influences the effectiveness of the therapy.

Furthermore, additional subgroup analyses will focus on the effects of the interventions across different stroke phases. Since participants are stratified based on the onset period of their stroke into acute to subacute, and chronic phases, these subgroup analyses will explore how the efficacy of the intervention varies between these two distinct stroke phases. We will perform regression analyses within each group stratified by the stroke onset period. If the statistical analysis reveals significant mean differences between various groups, post-hoc tests will be conducted to identify the specific groups among which these differences exist. This approach will provide valuable insights into whether the timing of a post-stroke intervention influences the efficacy of digital speech therapy. No interim analyses are planned to maintain the integrity of the non-inferiority margin or control for type I error rate.

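### The hypotheses carry a margin of +19 where non-inferiority needs −19, so the printed alternative is superiority of the app by at least 19 points

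*Protocol article*

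**What the plan says.** All of the relevant text is in the protocol article, mainly section 2.7 (Analysis).

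- **Hypotheses.** They are displayed as "H_{0}:\mu_{t}-\mu_{c}<\delta \;vs\;H_{1}:\mu_{t}-\mu_{c}\geq \delta".
- **Terms.** The symbol μt stands for the app arm: it "is the mean change in speech intelligibility score in the intervention group using the digital speech therapy application". The symbol μc denotes the same quantity for the workbook arm.
- **Margin.** δ "is set at 19 points, based on the assumption that a difference of 1 to 19 points" on the intelligibility scale is clinically non-inferior. It is given as a plain positive number.
- **Planning assumption.** "It is assumed that there is no difference between the two groups", followed by the statement that non-inferiority is what the study seeks to establish.
- **Error rates.** The plan describes "setting the significance level (alpha) to 0.025 for a one-sided test" and "targeting a power of 80" percent, with a standard deviation of 24.9, giving 28 per group.
- **Direction of the score.** Section 2.6.1 (Outcomes) compares transcriptions with the original passage to "calculate the percentage of correctly transcribed words", so a higher score is better and a positive μt − μc favours the app.

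**The concern.** Putting δ = 19 into the displayed hypotheses gives H0: μt − μc < 19 against H1: μt − μc ≥ 19. That is a test of superiority by a 19-point margin. Non-inferiority requires ruling out that the app is worse by 19 points or more, so the bound belongs at −19.

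The printed form conflicts with its own section in two ways. The assumed true difference of 0 falls inside H0, so the trial is planned under its own null. Every true difference in which the app is worse by less than 19 points, which is what the margin is meant to tolerate, also falls inside H0.

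The primary decision threshold is at stake. The article promises 95% confidence intervals but does not say which limit is compared with which bound. The tests listed afterwards (t-test or Mann–Whitney, mixed ANOVA, a 0.05 benchmark) are not tied to a margin. Nothing else in the text therefore corrects the sign.

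**Working it through.** **Inputs** (section 2.7): SD σ = 24.9; |δ| = 19; true difference 0; one-sided α = 0.025 (z = 1.960); power 80% (z = 0.842); 28 per group before dropout and 38 per group recruited.

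**Step 1. Reproduce the plan's n.** With the plan's formula,

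n = 2(z_α + z_β)²σ² / (μt − μc − δ)² = 2 × (1.960 + 0.842)² × 24.9² / 19² = 26.96,

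which rounds up to 27 per group. The noncentral t version gives power 78.6% at 27 and 80.1% at 28, so it yields exactly the plan's 28.

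**Step 2. Check whether n depends on the sign.** With μt − μc = 0 the denominator is (0 − 19)² = 361 for δ = +19, and (0 + 19)² = 361 for δ = −19. The sample size is the same, so agreement with 28 says nothing about which sign was meant. The form (μt − μc − δ) does fit the displayed hypotheses as a non-inferiority test if δ is a signed quantity equal to −19.

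**Step 3. Standard error.** SE = 24.9 × √(2/28) = 6.65.

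**Step 4. Compare the two thresholds at a true difference of 0, 28 per group** (normal approximation). Success means that the lower limit of the two-sided 95% interval for μt − μc exceeds the bound.

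| | Bound +19 (as printed) | Bound −19 (as intended) |
|---|---|---|
| Observed difference needed | 19 + 1.96 × 6.65 = +32.0 | −19 + 1.96 × 6.65 = −6.0 |
| Probability of success | Φ(−19/6.65 − 1.96) = 7.4 × 10⁻⁷ | Φ(19/6.65 − 1.96) = 81.5% (80.1% by noncentral t) |

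For 80% power against +19, the true advantage of the app would have to be 19 + (1.960 + 0.842) × 6.65 = 37.6 points.

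**Step 5. Repeat at the full 38 per group.** SE = 24.9 × √(2/38) = 5.71. The probability of success is about 6 × 10⁻⁸ against +19 and 91.4% against −19. Retaining every recruited participant does not change the picture.

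The gap between the two success thresholds is 32.0 − (−6.0) = 38 points, twice the margin.

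**The case against.** The best defence is that this is one missing character. If δ is read as −19, the displayed hypotheses and the formula's denominator agree and need no rewriting; only the prose, which gives the margin as a magnitude, lacks the sign. The intent is not in doubt: the abstract, the introduction, section 2.1 and section 2.7 all describe a non-inferiority trial, and calling a difference of 1 to 19 points non-inferior would make no sense under superiority by 19. The article also never says that a confidence limit will be compared with +19, so the 7-in-10-million figure rests on a decision rule supplied here. A full protocol or SAP may state the sign correctly.

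Much of this stands. The cause is very probably a dropped minus sign, n is unaffected, and the probability describes the literal reading, not an expected outcome. Placing the equality in H1 instead of H0 is untidy but has no numerical effect.

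The defence does not remove the error. The hypothesis line is the article's only formal statement of the primary criterion, and with the stated value of δ it is wrong. Because no confidence-limit rule is given elsewhere, a reader must correct the line before it can be applied. A primary criterion should not depend on inference, least of all one settled after results are known.

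**Conclusion.** The concern holds. As printed, the primary hypotheses describe superiority of the app by 19 points, contradicting the non-inferiority objective and the zero-difference assumption in the same section. Under the plan's own inputs (SD 24.9, 28 per group, true difference 0, one-sided 0.025), the literal criterion would be met with probability about 7 × 10⁻⁷, against about 80% for the evident intent. The stated 80% power therefore belongs to hypotheses other than those displayed. These figures assume that success is judged by the lower 95% confidence limit and that change is week 4 minus baseline with higher scores better. The sample size of 28 per group stands. The correction must be made because it concerns the primary success criterion, although the underlying design is recoverable.

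**What to change.** In section 2.7:

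1. Define change as week 4 minus baseline, with higher scores better.
2. State H0: μt − μc ≤ −19 versus H1: μt − μc > −19. This also puts the boundary value in H0.
3. Write the sample-size denominator as (μt − μc + 19)². Alternatively, keep the displayed formula and define δ = −19 throughout. Use one convention only.
4. Add the decision rule: non-inferiority is concluded if the lower limit of the two-sided 95% confidence interval for μt − μc lies above −19.

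Check that any full protocol or SAP carries the same sign and rule, and make the correction before unblinding. The cost is a few lines of text, with no change to the sample size, power or data collection.
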